## Methods

The proposed study is a part of a larger study, looking at brain and neurocognitive outcomes among male and female children and youth with various acquired brain injuries approved by both Sheba Medical Center (#3211-16-SMC) and Ministry of Health ethics (#20162005) committees, and was registered at the National Institute of Health (*NIH#*: *NCT03034031*). The unique data to be especially collected for this study includes sensitive puberty measures enabling a thorough examination of their effect on brain and neuropsychiatric outcomes and was preregistered in Open Science Framework (https://doi.org/10.17605/OSF.IO/FZWCE, version #1, 08/22). Data will be deidentified, saved with password and stored in a secured Hospital Server, with access limited to study research team. Trained clinic staff will describe the purpose of obtaining blood samples and MRI images, steps taken to protect the participant’s confidentiality and privacy in terms of how images and records would be managed and how research would be presented, a description of the MRI procedure, and a discussion of how participant safety would be maintained. All participants will enter voluntarily, their parents will sign a written informed consent form and the female participants will sign a written assent form indicating their understanding and acknowledgment of study’s procedures. The form will include an approval to share de-identified clinical data in adherence with local Institutional Review Board and other local ethical policies aimed at protecting patient privacy.

### Research design

The proposed study will use a longitudinal prospective design and follow females after pTBI and age matched healthy female controls, aged 9 to 16 years [47]. Participants will be followed from admission to 18 months post injury. Participants will undergo an MRI protocol, a short neuropsychiatric assessment and a clinical assessment of puberty stage and hormonal level, across two time points: **Acute (T0)**: within one month post injury; **Chronic (T1)**: 18 months from T0 (sufficient time for neuropsychiatric changes post pTBI [48]). For a description of the schedule of study’s enrolment and assessment periods see S1 Table.

### Sample size and power

Sample size was calculated on the basis of our primary hypothesis that puberty will moderate the associations between brain network connectivity measures, and neuropsychiatric outcome in females post pTBI. The bootstrap method for moderated-mediation models was used [49]. The bootstrap method, based on resampling, is useful for finding the standard errors and forming percentile-based confidence intervals (CIs) for estimates when their sampling distributions are unknown. According to Preacher, Rucker & Hayes (2007), a minimum of 100 participants are required in order to achieve power of at least .80, at a significance level of α = .05, with a Cohen’s d medium effect size (corresponding to a value of 13% of the variance in predicted variable [50]; and in accordance with previous studies on neural correlates of neuropsychiatric outcomes in children with TBI [51]). Based on the literature on longitudinal studies with pTBI patients, and due to technical issues such as unusable scans due to excessive movement anticipated in a pediatric study, we anticipate an attrition rate of ≈20% [52]. Thus, 120 female participants will be recruited: 60 with pTBI and 60 healthy controls.

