### Mediator

#### Changes in network brain connectivity

A score indicating differences in brain network connectivity measures between T1 and T0 will be defined and used as the mediating variable in all analyses. Children will be scanned on a 3T Magnetom Prisma (Siemens Healthineers) MRI system. Structural scans, T1-weighted, fluid attenuation inversion recovery (FLAIR) and susceptibility-weighted imaging (SWI) will be acquired for clinical neuroradiology report. During scans, participants will watch animated videos, in order to achieve better compliance in the scanner.

*Structural connectivity*. Will be measured using a diffusion weighted imaging scan. Spin-echo diffusion-weighted, echo-planar imaging sequence will be performed with 76 axial slices, voxel size 2x2x2mm, FOV = 240x240, matrix = 120x120, TR = 4500ms, TE = 51ms, MB = 2; b-value = 1,000 s/mm^2^, 64 gradient directions, 3-b0 images. Regularization, brain extraction, and motion correction will be conducted. Diffusion tensors will be calculated using a nonlinear regression procedure [53]. Whole brain tractography will be performed based on deterministic streamline fiber tractography approach [54].

*Brain network architecture of structural connectivity*. Using Brain connectivity toolbox, structural connectivity matrices will be calculated, by which, nodes indicating anatomical elements (brain regions) and edges, representing the relationships between nodes (white matter tracts), will be defined. These connectivity matrices will be further used for graph theory analyses, allowing to quantitatively characterize the global organization via network measures [55]: (1) **centrality**: strength (number of fibers connected to each node) and betweenness centrality (number of shortest paths passing through the target node); (2) **integration**: global efficiency (the shorter the path between two regions, the more efficient the connection), and (3) **segregation**: local efficiency and cluster coefficient: (reflects the tendency of nodes to cluster together). Lesions will be classified using a scheme of Adams et al. (1989) [56], to identify 3 diffuse axonal injury grades. We will further assess the relationships between network measures and the lesion grading score [57].

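### The 20% attrition allowance was added to 100 rather than divided out, so 120 recruits leave about 96 evaluable, 4 below the plan's stated minimum

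*Protocol article*

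**What the plan says.** Under the heading Sample size and power, the protocol article ties the calculation to its primary hypothesis, that puberty moderates the link between brain network connectivity and neuropsychiatric outcome. Citing a methods source on moderated mediation, it says "a minimum of 100 participants are required in order to achieve power of at least .80", "at a significance level of α = .05", for a medium effect equated with 13% of variance.

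It then gives two reasons for expecting losses, the experience of longitudinal studies in this population and scans spoiled by movement, and says "we anticipate an attrition rate of ≈20" per cent. The conclusion follows directly: "Thus, 120 female participants will be recruited: 60 with pTBI and 60 healthy controls".

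The Methods paragraph of the Abstract repeats 120, with 60 per group. No other section gives a different attrition rate, a larger target or a rule for replacing participants who are lost.

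**The concern.** The three figures are offered as one chain: a required number, an expected loss, and the number to recruit that follows. The last does not follow from the first two. The section calls 100 a minimum for the stated power, so an expected evaluable sample below 100 means that the power statement is not met under the plan's own assumption.

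The evaluable count is the right one to compare with 100. The section on changes in network connectivity says "A score indicating differences in brain network connectivity measures between T1 and T0 will be defined and used as the mediating variable in all analyses". A participant without a usable scan at both visits therefore has no observed mediator value, and the sample size section itself treats unusable scans as losses.

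At stake is the accuracy of the only sample size justification in the document. No estimand or analysis is affected.

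**Working it through.** **Inputs, all from Sample size and power**

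- Required number, total: 100
- Attrition, including unusable scans: about 20%
- Number to recruit: 120, as 60 + 60
- Power at least .80, α = .05

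**Reproducing the plan's figure**

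- Required × (1 + attrition) = 100 × 1.20 = 120. This matches exactly.
- Required / (1 − attrition) = 100 / 0.80 = 125. This does not match.

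The stated 120 is therefore the additive allowance. It takes 20% of the number required, whereas attrition acts on the number recruited.

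**What 120 delivers**

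- 120 × (1 − 0.20) = 96 evaluable in total, and 100 − 96 = 4 short.
- Per group: 60 × 0.80 = 48, if both groups lose the same fraction. The plan gives one overall rate, so the split is an assumption.

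**Attrition at which 120 is enough**

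- 1 − 100 / 120 = 0.167, or 16.7%.

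Because the rate is approximate, a range:

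| Attrition | Evaluable from 120 |
|---|---|
| 15% | 102.0 |
| 16.7% | 100.0 |
| 18% | 98.4 |
| 19% | 97.2 |
| 20% | 96.0 |
| 22% | 93.6 |
| 25% | 90.0 |

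**Number to recruit that keeps 100 at 20%**

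- 100 / 0.80 = 125.
- For equal groups, 126 (63 + 63): 126 × 0.80 = 100.8.

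**Size of the power loss (assumption)**

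Suppose 100 gives exactly 80% power for one parameter in a two-sided test at .05, by the normal approximation.

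- Standardised effect at 100: 1.960 + 0.842 = 2.802.
- At 96: 2.802 × √(96/100) = 2.802 × 0.980 = 2.745.
- Power: Φ(2.745 − 1.960) = Φ(0.785) = 0.784, about 78%.
- Loss: 80 − 78.4 = 1.6 percentage points.

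The 100 itself cannot be rebuilt. It comes from a cited source, and the article gives no path coefficients for the moderated-mediation model. The check takes 100 as the plan's own figure and does not depend on re-deriving it.

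**The case against.** The strongest reply is that both inputs are soft. The attrition rate is approximate, and 100 is a round number for power of at least .80, so the real power at 100 may exceed .80 and 96 may still be adequate. Part of this stands: the 78% is conditional on 100 giving exactly 80%, and the document does not allow a firmer figure. It does not remove the inconsistency. Rates of 17% or more leave fewer than 100, so 18%, 19% and 20% all fall short, and the section itself calls 100 the minimum.

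It could also be said that the analysis plan, which is not shown, may keep participants with one missing scan by imputation. That may be so and is not criticised here. The sample size section nevertheless counts such participants as lost, and its own figures should agree on that basis.

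A reader might infer more than the documents support:

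- **That far fewer than 96 will remain.** One could treat the 20% as drop-out alone and subtract failed scans at each visit on top. The section already names unusable scans as a reason for the 20%, so this counts them twice, and no separate scan-failure rate is given.
- **That needing two scans makes the gap wider still.** Losses above 20% would indeed leave fewer, but that is true of any plan whose assumption fails. It is not an error in this one.
- **That the study is seriously underpowered, or that enrolment must rise.** A gap of 4 participants, worth about 1.6 points of power under the stated assumption, does not carry that conclusion.

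**Conclusion.** The point holds as an arithmetic error. The expected evaluable sample is about 96, not 100, because the allowance was multiplied on rather than divided out. The shortfall of 4 evaluable participants corresponds to 5 recruits (125 − 120), or 6 for equal groups.

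This rests only on the plan's own 100, 20% and 120. The size of the power loss rests on the further assumption set out in the working and should be read as an indication. Severity is minor to moderate: the power statement for the primary hypothesis is not met as written, but the difference is small and easily corrected.

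**What to change.** Either of two changes to the sample size section would make it consistent:

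1. State that 120 recruits at about 20% attrition are expected to leave about 96 evaluable participants, and that power is then slightly below .80. The sponsor should recompute the power at 96 from its own model inputs; the 78% above is only a placeholder. This costs a sentence, one calculation and a slightly less favourable power figure.
2. Keep 120 and state that it supports 100 evaluable only if attrition is at most 16.7%. This costs a sentence, but it relies on a lower rate than the one the section cites, so it needs a reason.

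For reference, holding 100 evaluable at 20% attrition would take 125 recruits, or 126 for equal groups, which is 5 or 6 more participants. Correcting the text does not require this. If the target is changed, the Abstract must be changed with it.

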### Measures of study variables

#### 1. Independent variable

*Clinical TBI group*. Participants will include females following mild to moderate-severe injuries. Patients will be recruited from the Pediatric Emergency Department, which treats ~200 children diagnosed with mild- TBI annually with ~30% females, and from Pediatric Rehabilitation Departments (PRD) of both Edmond and Lily Safra Children’s Hospital, Sheba Medical Center and Loewenstein Hospital, Israel. Each department treats ~35 pTBI patients annually with ~30% females.

Injury severity will be defined based on a composite index according to child’s Glasgow Coma Scale (GCS), Duration of Post Traumatic Amnesia (PTA) and duration of Loss of Consciousness. As no single measure of injury severity has been found to be reliable among children, using an index score will allow us to define injury severity as a continuous variable ranging from complicated-mild to severe with greater accuracy.

*Healthy control group*. Healthy age matched female participants will be recruited from the general population or from siblings of pTBI females.

Inclusion criteria: 1. for pTBI: All injury severities; 2. For both pTBI and healthy controls: Females aged 9–16 years (based on the 95%CI of age range sensitive for attaining pubertal milestones) [47]. Exclusion criteria for both groups: 1. History of neurological disorders, intellectual disorders, developmental disorders or previous head injury; 2. Cardiovascular instability; 3. Fever or evidence of microbiological contamination; 4. Uncontrolled seizures; 5. MRI exclusion criteria, such as metal implants. 6. Endocrinology exclusion parameters: known abnormality of gonadotrophin secretion or of ovarian function. In addition, all MRI scans will undergo a neuroradiological examination, and abnormal findings (aside from their brain injury for the pTBI group), will be reported to the Institutional Ethics Committee as well as to the participant. Following this, participant’s participation in the study will be stopped.

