Hormonal dysfunction following pTBI is common and can evolve, resolve, or persist after injury [31]. It is not clear how much of the puberty related hormonal changes contribute to variation in pTBI outcomes [31]. Puberty is a key developmental milestone accompanied by substantial physical growth, neurologic changes, peak levels of sex hormones, and changes in emotional and behavioral symptoms [32]. It encompasses a combination of two distinct brain activated hormonal processes, adrenarche (the activation of the HPA axis) and gonadarche (the reactivation of the hypothalamic-pituitary-gonadal axis), which together lead to a dramatic rise in the circulating levels of sex hormones [33]. Puberty is associated not only with an increase in hormone levels, but also with dramatic fluctuations in the levels of estrogen circulating in the body [34]. Subsequently, the body’s systems must rapidly adapt to higher and fluctuating levels of hormones that may influence mood and other emotional symptoms. Recently, a large cohort study [35] demonstrated that earlier onset of puberty (pubescence) was associated with higher risk of depression and anxiety in females but was unrelated to the presence of depression in males. The gap between the onset of emotional changes and full maturation of inhibitory brain mechanisms may contribute to a window of risk for emotional dysregulation and other neuropsychiatric symptoms during puberty [36]. Paucity of studies have indicated that pubertal status predicts sex difference in the prevalence of neuropsychiatric symptoms better than age, suggesting that sex hormones play a significant role in the pathophysiology of neuropsychiatric disorders [34]. Furthermore, it should be acknowledged that age and pubertal maturation are highly correlated, arising the need for research designs that explicitly disentangle puberty and age effects on pTBI outcomes [37]. This requires the comparison between females with and without pTBI within the same age range and puberty phase.

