#### Descriptive statistics

Descriptive statistics of variables will be obtained to understand the characteristics of the study population, to evaluate the distribution of participants across subgroups (e.g., puberty stage), and to identify potential confounders to inform subsequent analyses.

**Aim 1**- **moderated-mediation model:** To test our main study’s hypothesis we will apply a moderated- mediation model. Briefly, we will examine whether the magnitude of a mediation effect impact of mediator (*changes in brain network connectivity*) on the association between predictor (*pTBI*) and outcome (*neuropsychiatric outcomes*) is conditional on the value of a moderator (*puberty stage at T0*). The analysis of the moderated-mediation model will use Hayes’s (2013) PROCESS macro (Model 59) [73]. Bootstrapping method will test significance of the effects to obtain robust standard errors for parameter estimation [73]. This will produce 95% bias-corrected confidence intervals of these effects from 1000 resamples of the data. Confidence intervals that do not contain zero indicate significant effects at *p* < .05.

**Aim 2- effect of changes in puberty stage and hormonal levels on mediator and outcome:** Two step-wise linear regression models controlling for age and pre/post-injury factors in the 1st step; for the injury severity in the 2nd step; and for puberty stage and hormonal levels at T0 and T1, as well as the difference between both measures (i.e., *Δpuberty stages and Δhormonal levels*) in the 3^rd^ step, to predict (1) brain network connectivity and (2) neuropsychiatric outcomes, at T1 will be conducted.

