#### Secondary analyses

For all analyses, an equal distribution assumption of potential confounders (participants’ age, injury severity, time since injury, and pre/post-injury factors) will be tested and models augmented with terms for these confounders will be considered.

Puberty stage: in our primary analyses, we will use a binary puberty score (pre/post pubescence). Secondary analyses will consider each of the puberty measures (PDS, hormonal levels, Tanner stage) separately.

Neuropsychiatric outcomes: our primary analyses will use a composite global neuropsychiatric risk score based on the ASEBA Summary scales as our main outcome. In secondary analyses, we will consider each of the neuropsychiatric measures (IR, ASEBA, Emotional Regulation) separately.

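### Sister controls are allowed, but the Aim 1 bootstrap makes no provision for families and the primary model has no age term

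*Protocol article*

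**What the plan says.** All references are to the protocol article.

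- **Source of controls** (Measures, Independent variable): "Healthy age matched female participants will be recruited from the general population or from siblings of pTBI females". No cap on siblings is given.
- **Matching** (Research design): the study will "follow females after pTBI and age matched healthy female controls, aged 9 to 16 years". Neither section says whether matching is by pair or by group, or gives an age tolerance.
- **Why age matters** (Introduction): the authors note that age and pubertal maturation move closely together and that designs must separate them. They conclude: "This requires the comparison between females with and without pTBI within the same age range and puberty phase".
- **Primary analysis** (Analytical approach, Aim 1 paragraph): a moderated-mediation model, PROCESS Model 59, with puberty stage at T0 as moderator. On inference: "This will produce 95% bias-corrected confidence intervals of these effects from 1000 resamples of the data". No family, pair or cluster term is named, and no age term.
- **Aim 2** (same section): the regressions control for age in their first step.
- **Age in Aim 1** (Secondary analyses): the balance of age and other confounders is tested, after which "models augmented with terms for these confounders will be considered".

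**The concern.** A case and her sister share family, genes, socioeconomic status and maternal education, and probably the parent who completes the CBCL. The primary outcome is a composite of the ASEBA summary scales, so that shared rater matters. Such pairs are correlated. A bootstrap that draws girls one at a time treats them as independent and so misstates the error of any contrast that sets cases against their sisters.

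Age is the second strand. A non-twin sister differs in age from her own case. If she counts as that girl's match, the match on age is loose, and her puberty stage may differ too. The Aim 1 model has no age term to absorb this, although the Introduction makes separating age from puberty a requirement of the design.

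At stake are the precision of hypotheses 1.1 and 1.2, the error rate of the puberty interaction, and how cleanly a puberty effect can be told from an age effect.

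**Working it through.** **Inputs from the article.** It gives no figure on this point. The sample size is the only relevant one: 100 × 1.20 = 120 reproduces the recruited number, 60 per group. After the anticipated 20% attrition, 120 × 0.80 = 96 remain, or 48 per group.

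**Assumed inputs.** None of these is in the article:
- f, the share of controls who are sisters of enrolled cases
- r, the within-family correlation
- q, the share of sister pairs discordant on the binary puberty score

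**Group contrast.** With n per group and f·n case-sister pairs, the variance of the mean difference is

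2σ²/n − 2·f·n·rσ²/n² = (2σ²/n)(1 − f·r).

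An analysis assuming independence uses 2σ²/n, so it overstates the standard error by the factor 1/√(1 − f·r).

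| f | r | 1/√(1 − f·r) | SE overstated by |
|---|---|---|---|
| 0.10 | 0.2 | 1/√0.98 | 1.0% |
| 0.25 | 0.3 | 1/√0.925 | 4.0% |
| 0.25 | 0.5 | 1/√0.875 | 6.9% |
| 0.50 | 0.3 | 1/√0.85 | 8.5% |
| 0.50 | 0.5 | 1/√0.75 | 15.5% |
| 1.00 | 0.5 | 1/√0.50 | 41.4% |

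A nominal 95% interval then covers 96.4% at f = 0.25, r = 0.5 and 97.6% at f = r = 0.5.

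The effective sample size forgone is 1 − (1 − f·r) = f·r. At f = 0.50 that is 0.15 to 0.25 for r = 0.3 to 0.5. The matching variance overstatement is 1/0.85 = 1.18 to 1/0.75 = 1.33.

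**Simulation check.** With 48 per group, 500 simulated trials and 400 resamples, individual against family bootstrap standard errors were:
- f = 0.25: 0.217/0.208 = 1.04 (r = 0.3) and 0.216/0.203 = 1.06 (r = 0.5)
- f = 0.50: 0.217/0.200 = 1.09 (r = 0.3) and 0.218/0.189 = 1.15 (r = 0.5)

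These agree with the formula. In a second simulation (50 per group, f = r = 0.5, q = 0.5), mean interval width fell from 0.766 to 0.660 when families were resampled. The ratio is 0.86, against √0.75 = 0.87.

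**Group-by-puberty interaction.** Concordant pairs reduce the variance and discordant pairs increase it. In balanced cells the factor is 1 − f·r(1 − 2q), and coverage is 2Φ(1.96/√factor) − 1. At f = r = 0.5:

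| q | Factor | Coverage of a nominal 95% interval |
|---|---|---|
| 0 | 0.75 | 97.6% |
| 0.5 | 1.00 | 95.0% |
| 0.7 | 1.10 | 93.8% |
| 1 | 1.25 | 92.0% |

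The interval is too narrow only when q exceeds one half. The article gives an average progression of 0.96 Tanner stages per year, so sisters two years apart (assumed) would differ by about 2 × 0.96 = 1.92 stages. Discordance is plausible, but its rate is unknown.

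**Age.** The Introduction asks for comparison within the same age range and puberty phase. Aim 2 adjusts for age at its first step. Aim 1, the primary analysis, names no age term, and the Secondary analyses section only considers one. Aim 1 therefore rests on matching whose unit and tolerance are not stated and whose control source includes sisters.

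**The case against.** The strongest reply is that much of this depends on what the article does not say.

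- **Resampling unit.** The article describes resamples of the data and never states that girls are drawn singly. Only a condensed article is at hand, and a preregistration exists that may say more. This stands in part: individual resampling is an inference. But the article does fix both the recruitment source and the inference method, and the described method makes no allowance for the source.
- **Matching.** A reader might infer that siblings cannot be age matched, so that the matching is broken. The text does not support that. Twins are the same age, one girl's sister can match another case, and matching may be at group level within 9 to 16 years. No pairing of a case with her own sister is stated. What remains is that age matching is not assured.
- **Direction.** A reader might infer a risk of false positives on the group contrasts. The error runs the other way: with positive correlation these intervals are conservative. The reported interval does not widen as sisters are added; an available gain in precision is left unused.
- **Size.** The general population is named first as a source, and an eligible sister must be a healthy girl aged 9 to 16, so the share may be small. The mediator is a change score, in which stable family differences partly cancel, so r may be below 0.3 for connectivity. At f = 0.10 and r = 0.2 the overstatement is 1.0%. It would also be wrong to read the 18 to 33% variance overstatement at f = 0.50 as lost sample size; that loss is 15 to 25%.
- **Age.** Its balance will be tested for all analyses, and puberty at T0, closely related to age, is in the model. Sibling age gaps can go either way and bias the contrast only if systematic, which is not shown. This is fair, but adjusting for puberty does not separate it from age, which is the article's own aim.

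**Conclusion.** The point holds as a modest one. Sisters of cases may be controls, and the described Aim 1 analysis neither allows for family dependence nor includes age.

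If case-sister pairs are enrolled and girls are resampled as independent, the group-contrast standard error is overstated by about 4 to 7% at a 25% sibling share and 8.5 to 15.5% at 50%, for r of 0.3 to 0.5. This costs precision and does not produce false positives. The group-by-puberty term is exposed to under-coverage only if more than half of sister pairs are discordant on puberty. All of these sizes rest on assumed shares, correlations and discordance rates, and they are small if sisters are few.

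The age strand does not depend on those assumptions. The primary model relies on age matching that is not specified closely enough to be assured for sister controls, while the article itself asks for age and puberty effects to be separated.

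**What to change.** 1. Record a family identifier at enrolment. In the Aim 1 bootstrap, resample families, or use family-clustered errors. This corrects the interval in either direction.
2. Include age at T0 as a covariate in the primary Aim 1 model, as Aim 2 already adjusts for age, rather than only considering it among secondary analyses.
3. Report the number of sibling controls, and state whether matching is by pair or by group and with what age tolerance.

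The cost is one extra data field and a short script in place of the macro's default bootstrap. No further participants or visits are needed, and age is already known. The real price is some loss of precision on the puberty terms, because age and puberty are correlated; that loss reflects how much the data can say about puberty apart from age.
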